## **2.0 RESEARCH QUESTION**

Will there be any differences in terms of sign and symptoms, hand function, occupational performance, and perceptions about splint wearability between patients diagnosed with trigger finger (TF) involving the A1 pulley who are prescribed a relative motion (RM) splint for six weeks and those who received a metacarpophalangeal joint (MCPJ) blocking splint under the same conditions?

## **2.1 HYPOTHESES**

Hypothesis 1: There is a difference in terms of severity staging as measured by Stages of Stenosing Tenosynovitis (SST) between patients diagnosed with TF involving the A1 pulley who are prescribed a RM splint for six weeks and those prescribed a MCPJ blocking splint under the same conditions.

Hypothesis 2: There is a difference in terms of pain as measured by Visual Analog Scale (VAS) between patients diagnosed with TF involving the A1 pulley who are prescribed a RM splint for six weeks and those prescribed a MCPJ blocking splint under the same conditions.

Hypothesis 3: There is a difference in terms of finger triggering as measured by number of triggering events in ten active fists between patients diagnosed with TF involving the A1 pulley who are prescribed a RM splint for six weeks and those prescribed a MCPJ blocking splint under the same conditions.

Hypothesis 4: There is a difference in terms of hand function as measured by Disabilities of the Arm, Shoulder and Hand (DASH) Outcome Measure between patients diagnosed with TF involving the A1 pulley who are prescribed a RM splint for six weeks and those prescribed a MCPJ blocking splint under the same conditions.

Hypothesis 5: There is a difference in terms of occupational performance as measured by Canadian Occupational Performance Measure (COPM) between patients diagnosed with TF involving the A1 pulley who are prescribed a RM splint for six weeks and those prescribed a MCPJ blocking splint under the same conditions.

Hypothesis 6: There is a difference in terms of comfort as measured by Visual Analog Scale (VAS) between patients diagnosed with TF involving the A1 pulley who are prescribed a RM splint for six weeks and those prescribed a MCPJ blocking splint under the same conditions.

Hypothesis 7: There is a difference in terms of satisfaction as measured by Visual Analog Scale (VAS) between patients diagnosed with TF involving the A1 pulley who are prescribed a RM splint for six weeks and those prescribed a MCPJ blocking splint under the same conditions.

## **2.2 RESEARCH OBJECTIVE**

### **2.2.1 General Objective**

To compare the effectiveness of RM and MCPJ blocking splints in terms of sign and symptoms, hand function, occupational performance, and perception of splint wearability (comfort and satisfaction) after six weeks of TF management.

### **2.2.2 Specific Objectives**

Specific Objective 1: To compare the effectiveness of RM splint and MCPJ blocking splint on TF severity after six weeks of TF management.

Specific Objective 2: To compare the effectiveness of RM splint and MCPJ blocking splint on pain after six weeks of TF management.

Specific Objective 3: To compare the effectiveness of RM splint and MCPJ blocking splint on finger triggering after six weeks of TF management.

Specific Objective 4: To compare the effectiveness of RM splint and MCPJ blocking splint on hand function after six weeks of TF management.

Specific Objective 5: To compare the effectiveness of RM splint and MCPJ blocking splint on occupational performance after six weeks of TF management.

Specific Objective 6: To compare the effectiveness of RM splint and MCPJ blocking splint on comfort after six weeks of TF management.

Specific Objective 7: To compare the effectiveness of RM splint and MCPJ blocking splint on satisfaction after six weeks of TF management.

## **3.0 METHODOLOGY**

### **3.1 Study Design**

This research will use a randomized comparative trial design with random assignment of participants into Relative Motion Group (RMG) that receives RM splint, or Metacarpophalangeal Joint Blocking Group (MCPJBG) that receives MCPJ blocking splint.

#### **3.1.1 Instrumentation**

##### **a. Demographic Questionnaire**

This self-developed questionnaire will be used to collect the participant's personal information, including age, gender, occupation, hand dominance, finger involved, associated medical conditions, and duration of triggering.

**b. Stages of Stenosing Tenosynovitis (SST)**

In this study, the Stages of Stenosing Tenosynovitis (SST) will be used to measure the participant's severity staging of TF. This is a grading system that divides TF into six stages with each stage is theorized to describe a different mechanical problem. Typically, Stage 1 is normal; Stage 2 is uneven finger movement; Stage 3 is triggering or clicking or catching; Stage 4 is locking of finger in flexion or extension, which can be unlocked by active finger movement; Stage 5 is locking of finger in flexion or extension, which requires application of passive force to unlock; and Stage 6 is locked finger in flexion or extension (Patel & Bassini 1992).

**c. Visual Analog Scale (VAS)**

The Visual Analog Scale (VAS) will be used to measure the participant's pain as well as comfort and satisfaction with splint wear in this study. VAS is a 10cm line that can be scored in either centimetres or millimetres (Dale et al. 2011). For pain, the left end of the VAS will be labelled as "no pain" and the right end "extreme pain". For comfort, the left end will be labelled as "not at all comfortable" and the right end will be labelled as "extremely comfortable". For satisfaction, the left end will be labelled as "not at all satisfied" and the right end will be labelled as "extremely satisfied". At the times of evaluation, each patient will be asked to make a mark on the line to indicate his/her rating for pain, comfort or satisfaction. The distance of this mark from the left end of the line will be measured. Thong et al. (2018) had reported that VAS pain scale had excellent internal consistency (Pearson's  $=0.93$ ) while Paungmali et al. (2012) reported that VAS had excellent test-retest reliability (Intraclass Correlation Coefficient, ICC= $0.90$ ). The minimal clinically important difference of the VAS pain scale is 12mm (Kelly 2001).

**d. Number of Triggering Events in Ten Active Fists**

Number of Triggering Events in Ten Active Fists will be used to measure the patient's triggering frequency (Finch et al. 2002). The number of triggering events (0 – 10) can be obtained by asking the patient to make 10 active full fists (Colbourn et al. 2008). Typically, this involves asking the patient to actively and fully open and close the fingers 10 times. If the finger persistently locks anytime during active finger opening and closing, a score of 10/10 will be assigned. If the patient has multiple TF per hand, he/she is only asked to open and close the fingers 10 times. The result is taken from the worst finger's performance. Time needed to make 10 active full fist will be recorded using a stopwatch or clock that reads in seconds.

**e. Disabilities of the Arm, Shoulder and Hand (DASH) Outcome Measure**

The Disabilities of the Arm, Shoulder and Hand (DASH) Outcome Measure will be used to measure hand function in this study. DASH is a 30-item, self-report questionnaire designed to assess the patient's health status during the previous week. The DASH consists of 21 items that assess performance of select activities; 5 items assess the severity of symptoms; and 4 items assess the impact of the problem on social function, work, sleep and self-image. Two optional modules specific to work, sports and/or performing arts will not be used in this study. The DASH has a total possible score of 0 to 100 with higher scores represent more severe disability or poorer hand function (Hudak et al. 1996; William 2014). The minimal clinically important difference for the DASH is 10.83 points (Franchignoni et al. 2014). Kleinlugtenbelt et al. (2018) reported excellent internal consistency (Cronbach's  $\alpha=0.97$ ) and excellent test-retest reliability (ICC= $0.91$ ) for the DASH.

## f. Canadian Occupational Performance Measure (COPM)

The Canadian Occupational Performance Measure (COPM) will be used to measure the participant's occupational performance. COPM, developed by the Canadian Association of Occupational Therapist, in collaboration with Health and Welfare Canada (Law et al. 1990), is a widely known interview-based assessment tool for measuring occupational performance. COPM uses a client-centered approach and requires the patient to report the types of activities that he/she is unable to accomplish and later, prioritize the meaningfulness and importance of the selected activities. During the interview, the patient must report and rate the satisfaction and the performance of the activities in three occupational therapy areas, i.e., self-care, productivity, and leisure. The importance, satisfaction, and performance of an activity are rated using a 10-point rating scale. A benefit of the COPM is that self-perceived changes in occupational performance problems can be assessed over time (Law et al. 1990). Berardi et al. (2019) found that COPM has good construct validity (Cronbach's  $\alpha=0.89$ ) and excellent test-retest reliability for the performance subtest (ICC=0.99) and the satisfaction subtest (ICC = 0.98). The minimal clinically important difference of the COPM is 3.0 points and 3.2 points for performance subtest and satisfaction subtest, respectively (Tuntland et al.2016).

[figure not shown]

[figure not shown]

Figure 1.0 CONSORT flow chart. This figure shows the flow of patients through the trial according to the criteria recommended in the CONSORT Guidelines.

### 3.2 Study Sample

Patients who are diagnosed with TF involving the A1 pulley by a surgeon in the Orthopaedic Clinic, Hospital Sultan Haji Ahmad Shah, Temerloh, Pahang; satisfy the inclusion criteria; and referred for TF management at the Occupational Therapy Unit of this same public hospital during the period 1 January 2022 – 31 December 2024.

### 3.3 Inclusion Criteria

The inclusion criteria are:

- aged  $\geq 21$  years
- single or multiple TF
- unilateral or bilateral TF
- neutral MCPJ position can be attained during passive isolated MCPJ extension of the affected finger

### 3.4 Exclusion criteria

The exclusion criteria are:

- trigger thumb
- steroid injection of the affected finger within last six months
- A1 pulley release of the affected finger.
- history of fracture, tendon injury, nerve injury, Dupuytren's contracture, and other soft tissue injuries of the affected finger or adjacent fingers.

### 3.5 Withdrawal criteria

Participants can choose to withdraw at any time. Participants may be withdrawn if the investigator deems that it is detrimental or risky for the subject to continue. Withdrawn subjects will not be replaced by a new participant as we have already included the dropout rate (10%) into our sample size calculation.

### 3.6 Sample Size

A sampling of convenient method will be used to select eligible patients.

A prior TF research study (Teo et al. 2019) had reported that the result of pain score for pre-treatment = 4.65 (SD 2.39) and post-treatment = 3.40 (SD 2.44). G\*Power was used to compute statistical power analyses. Cohen-d effect size is 0.5175152.

Given Cohen-d effect size needs to be converted into Cohen-f effect size in order to determine the sample size of this study for two ways ANOVA, therefore, after converting digitally, the Cohen-f effect size is 0.259.

This proposed study will need 32 participants when a Cohen-f effect size of 0.26, confident level of 95%, significant level of 5%, and statistical power of 80% is applied.

Since a 10% dropout rate is anticipated, a total of 36 participants will be needed for this study. Of this total, 18 patients will be allocated to the RM group (RMG) and 18 patients to the MCPJ blocking group (MCPJBG).

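### Section 3.6 sizes a comparison of two splints with an earlier study's pre-to-post change in pain, so the stated 80% power does not apply to a between-splint difference of that size (about 29%)

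*Protocol*

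**What the plan says.** Section 3.6 takes its effect size from one earlier trigger finger study, reported as "pre-treatment = 4.65 (SD 2.39) and post-treatment = 3.40 (SD 2.44" at the second assessment. It then states that "Cohen-d effect size is 0.5175152" and that "after converting digitally, the Cohen-f effect size is 0.259". The conversion is made "in order to determine the sample size of this study for two ways ANOVA". The result is "This proposed study will need 32 participants when a Cohen-f effect size of 0.26", with "significant level of 5%, and statistical power of 80% is applied". A 10% dropout allowance raises 32 to 36, or 18 per arm.

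The seven hypotheses in section 2.1 and the specific objectives in section 2.2.2 all compare the relative motion splint with the MCPJ blocking splint. Section 3.9 tests them with a two-way mixed ANOVA. Pain is measured twice, on Day 1 and at Week 6. Section 3.1.1(c) adds a benchmark for pain: "The minimal clinically important difference of the VAS pain scale is 12mm".

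Section 3.6 gives no between-splint difference as its target, no pre-post correlation, and no name for the G*Power test.

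**The concern.** The two means in section 3.6 are the same patients' pain before and after treatment. Their difference measures how much patients improve, not how much better one splint is than another. Two active splints can both produce that improvement and differ little between themselves.

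The 80% is the protocol's only statement of what the trial can detect. If it belongs to a different question, readers will take a non-significant splint comparison as coming from an adequately powered trial when it did not. A difference as large as the earlier study's whole improvement would more likely be missed than found over most of the plausible range of correlations.

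**Working it through.** **Inputs.** From section 3.6: means 4.65 and 3.40, SDs 2.39 and 2.44, f = 0.26, N = 32, alpha 0.05, two equal groups. From section 3.8: two pain assessments. From section 3.1.1(c): 12 mm, which is 1.2 on a 10 cm line. Assumed, because the protocol does not give it: pre-post correlation rho, taken as 0.5 with a range of 0.3 to 0.8.

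**Step 1: the protocol's effect size.**
- SD = sqrt((2.39² + 2.44²)/2) = 2.415
- d = (4.65 − 3.40)/2.415 = 1.25/2.415 = 0.5176
- f = d/2 = 0.2588, rounded to 0.26

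This agrees with section 3.6 and confirms that d is a change over time.

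**Step 2: the protocol's sample size.** For a repeated-measures ANOVA with 2 groups and m = 2 times, both the time effect and the group-by-time interaction use

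lambda = f² × N × m/(1 − rho), on 1 and N − 2 degrees of freedom.

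With f = 0.26, N = 32 and rho = 0.5, lambda = 0.0676 × 32 × 2/0.5 = 8.65 and power is 81.2%. N = 30 gives 78.5%, so 32 is the smallest even N. Dropout: 32/0.9 = 35.6, so 36.

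Other routes:

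| Test | N for 80% power |
|---|---|
| Time or interaction, rho 0.5 | 32 |
| Paired t-test on d = 0.5175 | 32 (81.0%; n = 31 gives 79.6%) |
| Time or interaction, rho 0.3 | 44 |
| Time or interaction, rho 0.7 | 20 |
| Between-group main effect, two times, rho 0.5 | 90 |
| One-way comparison of two groups | 120 |

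**Step 3: what f = 0.26 means under each reading.**
- *Time effect.* Each time mean lies f × SD from the overall mean, so the change is 2 × 0.2588 × 2.415 = 1.25 points. The 80% is then power to show that patients improve.
- *Interaction.* Each of the four cells deviates by f × SD, so the between-splint difference in change is 4 × f × SD. With f = 0.26 this is 1.04 SD, or 4 × 0.26 × 2.415 = 2.51 points. With the unrounded f = 0.2588 it is 2.50 points, exactly 2 × 1.25.

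**Step 4: power for the splint comparison.** Put f = difference/(4 × 2.415) into the formula in step 2. For 1.25 points, f = 0.1294 and lambda = 0.01674 × 128 = 2.14 (rho 0.5). For 1.2 points, f = 0.1242 and lambda = 1.98.

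| Difference in change, N = 32 | rho 0.3 | rho 0.5 | rho 0.7 | rho 0.8 |
|---|---|---|---|---|
| 2.5 points (1.04 SD) | 67% | 81% | 96% | 99% |
| 1.25 points (0.52 SD) | 22% | 29% | 45% | 61% |
| 1.2 points (0.50 SD) | 21% | 27.5% | 42% | 58% |

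A simulation of 100,000 trials at rho = 0.5 gave 80.9% for 2.5 points and 29.3% for 1.25 points.

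**Step 5: other sample sizes.** At rho = 0.5, power for 1.25 points is 33% with 36 evaluable and 37% with 42. Reaching 80% would take about 120 evaluable (118 gives 79.6%, 120 gives 80.3%).

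**The case against.** The strongest reply is that nothing in section 3.6 is miscalculated: d, f, 32 and 36 all follow from each other once rho = 0.5 is granted. That stands. The fault lies in what the effect represents.

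A reader might infer that the protocol entered the earlier change as the between-splint interaction. The document does not support that. It names only a two-way ANOVA and G*Power, the time effect gives the same N, and so does a paired t-test. For change over time, 32 participants do have about 81% power for 1.25 points at rho = 0.5. This does not rescue the claim, because no hypothesis asks whether patients improve, and power for the splint comparison is the same whichever option was chosen.

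The 1.25 points is not a between-splint target, and section 3.1.1(c) does not offer 12 mm as one. Both serve here only as yardsticks that the protocol itself supplies. The 12 mm yardstick also mixes scales. Section 1.2 lists what appears to be the same earlier study among those using a numerical pain rating scale, whereas this trial uses a 10 cm VAS. The 1.2-point figures therefore assume that an SD of about 2.4 carries over.

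A reader might also infer that the trial would declare the splints equivalent after a null result. No section plans that.

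Baseline-adjusted analysis would help somewhat, but it is not planned. With SD × sqrt(1 − rho²) as the residual SD and 29 degrees of freedom, power for 1.25 points at N = 32 is about 32% to 65% over rho 0.3 to 0.8, still short of 80%.

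**Conclusion.** Wrong as written. Section 3.6 attaches 80% power to an effect that is not the one under test. At 32 evaluable participants and rho = 0.5, 80% power for the splint comparison requires a difference in change of about 1.0 SD (2.5 points), and no between-splint figure in the protocol supports a difference that large. Power is about 29% at 1.25 points and about 27% at 1.2 points. The size of the shortfall depends on rho, which is an assumption; no value from 0.3 to 0.8 brings power for either difference above 61% at N = 32. The result at 1.2 points also rests on the SD carrying over between pain scales. Which G*Power option was used remains unknown and does not alter the conclusion.

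**What to change.** Reword section 3.6 as follows:
- Remove the claim that 80% power follows from the earlier study's pre-post effect. Acknowledge that f = 0.26 was derived from a change over time and that no between-splint difference supports it.
- State that 32 evaluable participants give about 80% power for a between-splint difference in change of about 1.0 SD. Name the test, the assumed pre-post correlation (0.5) and the source and scale of the SD.
- Give the power at about 0.5 SD, roughly the 12 mm benchmark: about 27% at correlation 0.5, and 21% to 58% over 0.3 to 0.8.
- Reconcile the target size, which is 42 in the synopsis and 36 in sections 3.6 and 3.7, and recompute these figures for the evaluable number that results.

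The cost is a change of text in one section plus the reconciliation of the target. No patients are added. The stated power becomes much less favourable, which is an accurate account of the design at its present size.

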### 3.7 Study Duration and Timeline

Stage 1, review of article 12 months

Stage 2, data collection and data analysis 24 months

Stage 3, presentation and publication 12 months

Each patient will be involved in this study for 8 weeks. The duration of complete recruitment of 36 patients is estimated to be 2 years.

### 3.8 Study Visits and Procedures

This study will adopt a randomized comparative trial design. This study will involve the researcher, a counter staff, Therapist A, and Therapist B. The researcher will do the eligibility screening and splint fabrication. The counter staff will be involved in random assignment of participants to either the RMG or the MCPJBG. Therapist A, an occupational therapist with 10-years of experience is not a research team member and will conduct the pre-intervention assessments at Day-1 and the post-intervention assessments at Week-6. Therapist B, a senior occupational therapist with 20-years of experience also is not a research team member and will involve in conducting the conventional therapy program and assessment at Week-3. Due to the nature of study and the visibility of splint wearing (Jackman et al. 2013), the participants, the researcher, Therapist A, and Therapist B will not be blinded to the intervention.

Patients who have been recently diagnosed as having TF involving the A1 pulley and referred by the Orthopaedic Clinic, Hospital Sultan Haji Ahmad Shah to the hospital's Occupational Therapy Unit will make a new patient appointment for occupational therapy. Therapy will be provided at the Occupational Therapy Unit. Patients with TF will have a designated appointment and will be registered in the hospital information system as a new outpatient by the counter staff. The researcher will receive notice of a potential participant through the hospital information system on registration, and a preliminary screening of each potential patient will be done by the researcher. This screening will include review of the electronic referral letter and the past electronic medical records entered by the orthopaedic surgeon. After the preliminary screen of the records, the researcher will ask the potential participant additional questions according to inclusion and exclusion criteria to insure study eligibility.

Once study eligibility is confirmed, the researcher will provide the information sheet and explain the study to the potential patient. If the patient agrees to participate, he/she will then be asked to sign the informed consent form and assigned an Identity Number (ID) for anonymity purposes. After signing the informed consent form, the Therapist A will proceed to administer the Demographic Questionnaire and other pre-intervention (baseline) assessments i.e., SST, DASH, COPM, VAS (pain, comfort, and satisfaction), and the Number of Triggering Events in Ten Active Fists. After completing the pre-intervention assessments, the participant will be asked to go to a designated counter near the therapy room for simple random assignment to the RMG or MCPJBG. Assignment will be done via concealed allocation with selection of an envelope by the counter staff. The envelope is prepared by the researcher. The envelope will contain either a paper printed with A which indicates RMG and B which indicates MCPJBG. After the participant returning to the therapy room, he/she will give the group assignment paper to the researcher. The researcher will fabricate either the RM splint or MCPJ blocking splint based on the randomization of group allocation. Each type of splint, the RM splint and MCPJ blocking will be fabricated using a low temperature thermoplastic material with 3.2 mm thickness, 1% perforation, and 100% memory.

For participants assigned to RMG, either a RME splint or a RMF splint will be fabricated. The splint design will be dependent on the participant's response to the RM pencil test carried out by the researcher. For this study, the RME pencil test will require the researcher to weave the pencil under the proximal phalanx of the affected finger(s) and over the dorsum of the adjacent fingers' proximal phalanx. For the RMF pencil test the researcher will weave the pencil over the dorsum of the proximal phalanx of the affected finger(s) and under the proximal phalanx of the adjacent fingers. With the pencil in place, the participant will be asked to open and close their fingers several times. The participant will be asked to choose which pencil test, RME or RMF lessened their pain and/or triggering. If the answer is the RME position, then a RME splint will be prescribed. Conversely, if the answer is the RMF position, then a RMF splint will be prescribed.

For the RME splint, a strip of thermoplastic will be woven around on the proximal phalanx of all four fingers with the MCPJ of the affected finger(s) positioned in approximately 20°-25° more extension than MCPJ of the adjacent fingers. For the RMF splint, the thermoplastic strip will be woven with the MCPJ of the affected finger(s) positioned in approximately 20°-25° more flexion than the MCPJ of the adjacent fingers. The angle of MCPJ will be increased if 20°-25° flexion/extension is not enough to reduce/stop pain or triggering. For MCPJ blocking splint, the thermoplastic material will be moulded to contour the palm over the MCPJ and formed into a circumferential "ring" around the proximal phalanx of the affected finger(s). After the splint was fabricated, the participants will have to wear the splint for 15 minutes to check if the splint has pressure points that can cause pain or any redness of the skin. If there are pain and redness, the splint will be readjusted to prevent these pressure points. For all splints, each participant will be asked to assess the comfort and satisfaction with the splint before leaving the clinic.

The RMG and MCPJBG participants will receive same education and conventional treatment. Each participant will be instructed to wear the splint full time (24-hours) every day and night for six weeks, with the exception that the splint can be removed for hygiene purposes including washing hands and showering. No gripping when out of splint. To track splint wearing adherence, each participant will be given a diary to record the hours the splint was worn in a 24-hour period. Participant will also be asked to record what task(s)he/she has

removed the splint. Each participant will be informed about the condition of TF including symptoms, cause, risk factor, and treatment. Participants will also be encouraged to modify activities that may provoke their TF symptoms while wearing the splint. Suggestions for activity modification include stopping or limiting activities that involve repetitive hand use and prolonged gripping. Participants will be asked to contact the researcher if there are any problems with the splint that affect wear or to replace the splint if participant has accidentally lost their splint. The researcher will arrange an appointment as soon as possible with them to address these problems and make note of this interruption in intervention.

Each participant will be required to attend three sessions of therapy over the study period of six weeks. These sessions ideally will be the initial therapy session (Week-1), then three weeks later (Week-3), and six weeks after the initial session (Week-6). At Week-3, Therapist B will conduct the VAS assessment (comfort, and satisfaction) and provide the conventional therapy to each participant. Therapist B will perform a deep circular massage over A1 pulley for 5 minutes and each participant will be taught how to do the deep circular massage at home. The researcher will inspect each participant's splint and adjust it accordingly based on the participant's comments.

At Week-6, Therapist A will administer the post-intervention assessment for all participants. Table 1.0 outlines the procedure involved in RMG and MCPJBG. Figure 1.0 is the flowchart of the procedure.

Table 1.0 Procedure involved in Relative Motion Group and Metacarpophalangeal Joint Blocking Group.

| Relative Motion Group (RMG)                                                                                                                                                                                                                                                                                                                                                                                                                                                                                                                                                                                                                                                                                                                                                                                                                                                                                                                                                                                                                                                                                                               | Metacarpophalangeal Joint Blocking Group (MCPJBG)                                                                                                                                                                                                                                                                                                                                                                                                                                                                                                                                                                                                                                                                                                                                                                                                                                                                                                                                       |
|-------------------------------------------------------------------------------------------------------------------------------------------------------------------------------------------------------------------------------------------------------------------------------------------------------------------------------------------------------------------------------------------------------------------------------------------------------------------------------------------------------------------------------------------------------------------------------------------------------------------------------------------------------------------------------------------------------------------------------------------------------------------------------------------------------------------------------------------------------------------------------------------------------------------------------------------------------------------------------------------------------------------------------------------------------------------------------------------------------------------------------------------|-----------------------------------------------------------------------------------------------------------------------------------------------------------------------------------------------------------------------------------------------------------------------------------------------------------------------------------------------------------------------------------------------------------------------------------------------------------------------------------------------------------------------------------------------------------------------------------------------------------------------------------------------------------------------------------------------------------------------------------------------------------------------------------------------------------------------------------------------------------------------------------------------------------------------------------------------------------------------------------------|
| Week 1 (Day 1)
Assessment 
 
Demographic questionnaire
 
Pre-intervention assessments               
 
DASH
 
COPM
 
VAS (Pain, Comfort, & Satisfaction)
 
Number of Triggering Events in Ten Active Fists
 
SST
 
 
 

Splint 
 
RME pencil test
 
RMF pencil test
 
Fabricate RME splint or RMF splint
 
MCPJ of the affected finger is approximately 20°-25° extension/flexion than the MCPJ of the adjacent fingers
 
Increase the angle if 20°-25° MCPJ extension/flexion of affected finger is not enough to reduce/stop the triggering/pain
 

Patient Education 
 
Splint wear full time for 6 weeks, only remove for hygiene purpose
 
No gripping when out of splint
 
Provide a diary to record everyday splint wear duration (hours)
 
Record what task the splint is removed for
 
About TF condition
 
 | Week 1 (Day 1)
Assessment 
 
Demographic questionnaire
 
Pre-intervention assessments               
 
DASH
 
COPM
 
VAS (Pain, Comfort, & Satisfaction)
 
Number of Triggering Events in Ten Active Fists
 
SST
 
 
 

Splint 
 
Fabricate MCPJ blocking splint
 
MCPJ positioned at 0°
 

Patient Education 
 
Splint wear full time for 6 weeks, only remove for hygiene purpose
 
No gripping when out of splint
 
Provide a diary to record everyday splint wear duration (hours)
 
Record what task the splint is removed for
 
About TF condition
 
Reduce or avoid activities such as repetitive hand use and prolonged grip or any action that causes pain/triggering
 
 |

|                                                                                                                                                                                                                                                                                                                        |                                                                                                                                                                                                                                                                                                                        |
|------------------------------------------------------------------------------------------------------------------------------------------------------------------------------------------------------------------------------------------------------------------------------------------------------------------------|------------------------------------------------------------------------------------------------------------------------------------------------------------------------------------------------------------------------------------------------------------------------------------------------------------------------|
| 
 
○ Reduce or avoid activities such as repetitive hand use and prolonged grip or any action that causes pain/triggering
 
                                                                                                                                                |                                                                                                                                                                                                                                                                                                                        |
| Week 3
Reassessment 
 
○ VAS (Comfort & Satisfaction)
 
 Conventional Therapy 
 
○ Deep circular massage over A1 pulley for 5 minutes
 
○ Review and adjust splint
 
                                     | Week 3
Reassessment 
 
○ VAS (Comfort & Satisfaction)
 
 Conventional Therapy 
 
○ Deep circular massage over A1 pulley for 5 minutes
 
○ Review and adjust splint
 
                                     |
| Week 6
Reassessment 
 
○ Post-intervention assessments 
 
- DASH
 
- COPM
 
- VAS (Pain, Comfort, & Satisfaction)
 
- Number of Triggering Events in Ten Active Fists
 
- SST
 
 
 
 | Week 6
Reassessment 
 
○ Post-intervention assessments 
 
- DASH
 
- COPM
 
- VAS (Pain, Comfort, & Satisfaction)
 
- Number of Triggering Events in Ten Active Fists
 
- SST
 
 
 
 |

